**Figure 1 F1:**
[figure not shown]
Schematic measurement schedule. Participants arrive fasting at 08:00, complete baseline assessments and consume a standardised breakfast. Breath VOC and capillary glucose samples are collected at fasted baseline and every ∼15 min during the first postprandial period. Subsequent meals (meals 2–4) are not standardised and are consumed voluntarily; breath VOC and glucose samples are collected immediately before each eating episode. VOC, volatile organic compound.

**Table 2 T2:** Schedule of study procedures

Procedure	Previsit	Visit day
Eligibility screening	X	
Informed consent	X	
Fasting and preparation instructions	X	
Diet and sleep diary (covering 2 days before visit)	X	Return (on or after visit)
Stool sample kit (collection within ±2 days)	X	Return (on or after visit)
Questionnaires (SF-36, IPAQ)		X
Body composition (BIA)		X
Oral microbiota swab		X
HbA1c (if not available <3 months in patient records)		X
Baseline breath VOC and capillary glucose		X
Standardised breakfast		X
VOC and glucose every 15 min (first 90 min)		X
VOC and glucose before subsequent meals/snacks		X

BIA, Bioelectrical Impedance Analysis; IPAQ, International Physical Activity Questionnaire; SF-3, 36-Item Short Form Health Survey; VOC, volatile organic compound.

### VOC and biospecimen collection

Breath samples are collected with a BreathSpec^®^ gas chromatography–ion mobility spectrometry system (GC-IMS). Capillary blood glucose is measured via fingerprick sampling using a Contour^®^ XT meter. Oral and stool samples undergo microbiota sequencing using established workflows. Raw instrument files and metadata are stored securely.

### Data sources and documentation

Study data include participant questionnaires, capillary glucose, breath VOC profiles, and oral and stool microbiota samples. All data collection instruments and source documents are summarised in table 3.

**Table 3 T3:** Data collection and source documents

Data item	Method/device	Source
Demographics, history, medication	Self-report	eCRF
SF-36, IPAQ	Standard questionnaires	eCRF
Body composition	Bioimpedance (InBody)	Device printout
HbA1c (if needed)	DCA Vantage®	Device record
Oral microbiota	OMNIGene^TM^ Oral Kit 16S-Seq.	Sequencing report
Stool microbiota	OMNIGene^TM^ Gut Kit 16S-Seq.	Sequencing report
Capillary glucose	Contour® XT metre	Device output
Breath VOCs	BreathSpec® GC-IMS	Instrument files
Diet/sleep diaries	Participant record	Diary/eCRF

eCRF, electronic Case Report Form; GC-IMS, gas chromatography–ion mobility spectrometry system; HbA1c, Glycated haemoglobin; IPAQ, International Physical Activity Questionnaire; SF-36, 36-Item Short Form Health Survey; VOCs, volatile organic compounds.

### Data management plan

Study data, including VOC instrument files, questionnaire data, capillary glucose values and microbiota sequencing outputs, are stored in secure institutional systems with role-based access. Source documents and metadata are maintained in REDCap with audit trails.

### Outcomes

The primary outcome is the temporal profile of VOC intensity across the 08:00–16:00 period. Secondary outcomes include differences across metabolic groups, associations between VOCs and capillary glucose ranges, and relationships between VOCs, body composition and microbiota profiles. The outcomes are summarised in table 4.

**Table 4 T4:** Outcomes

Outcome type	Description
Primary	Temporal variation in breath VOC intensities (08:00–16:00)
Secondary	Between-group comparisons (no diabetes, T1D, T2D)
	Associations between VOCs and capillary glucose
	Links between VOCs, body composition and microbiota

T1D, type 1 diabetes; T2D, type 2 diabetes; VOCs, volatile organic compounds.

### Sample size

A total of up to 60 participants will be enrolled, initially targeting approximately 10 per group, with variation in sex and BMI where possible. Recruitment aims for an approximate balance by sex and by BMI category (<25 vs ≥25 kg/m²). After around 30 participants, an interim exploratory assessment will be performed to evaluate whether discernible temporal patterns are present in the VOC data. If no circadian intensity changes are observed in at least three VOCs, the study will be stopped early; otherwise, recruitment will continue to the planned maximum of 60 participants. No formal hypothesis testing or statistical stopping rules are applied, as this is an exploratory study.

### Data processing and analysis

Data are processed using VOCal (GAS Dortmund) with retention index libraries (eg, NIST2020) and drift-time alignment. Analysis uses Python (gc-ims-tools) and R. Temporal VOC intensity profiles will be characterised descriptively across the 08:00-16:00 window, and within-subject changes over time will be assessed using non-parametric repeated-measures approaches appropriate for the data structure. Gallery plots will support visual inspection of spectral patterns. Between-group comparisons will include both overall group differences and exploratory pairwise comparisons (no diabetes vs T1D, no diabetes vs T2D, and T1D vs T2D), using appropriate non-parametric tests (eg, Wilcoxon rank-sum or Kruskal-Wallis). Given the exploratory design and limited consistency in prior findings, no single comparison is prioritised a priori. Associations between VOCs and capillary glucose, body composition and microbiota composition will be assessed using correlation analyses, including repeated-measures correlation for intraindividual relationships. For between-group VOC discrimination, supervised multivariate methods including Partial Least Squares Discriminant Analysis (PLS-DA) and Support Vector Machine (SVM) may be applied as exploratory tools, building on approaches previously used with GC-IMS breath data in this study population.^8^ Principal component analysis supports dimensionality reduction and visual exploration of VOC patterns. No imputation is planned.

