## Methods and analysis

### Study design and setting

This prospective, single-centre observational study is conducted in the clinical study facilities at the Diabetes Center Berne (DCB), Switzerland. Each participant completes one 8-hour study visit. The study aims to estimate daytime breath VOC dynamics rather than test a formal intervention or treatment effect.

Recruitment began in 2023, with data collection completed for three participants. The study has been paused since June 2024 due to device unavailability and resumed in December 2025. No interim analyses have been conducted to date. Enrolment is expected to conclude by October 2026, with primary data analysis completed within approximately 6 months thereafter.

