### Study procedures

Participants are instructed to fast from midnight before the study visit and to abstain from alcohol for 24 hours prior to the visit. On the morning of the visit, they are asked to avoid using toothpaste and mouthwash for at least 1 hour before the first measurement and, if possible, to refrain from using cosmetic products such as make-up, shampoo or perfume.

At 08:00, participants complete questionnaires (36-Item Short Form Health Survey (SF-36), International Physical Activity Questionnaire (IPAQ)) and undergo bioimpedance body composition analysis (BIA; InBody 770). HbA1c is measured on site only if no recent result (<3 months) is available from the patient record, using a DCA Vantage analyser (Siemens) according to the manufacturer’s instructions. Two fasting breath samples and one capillary glucose measurement are then collected. Participants subsequently provide an oral microbiota swab and consume a standardised breakfast (YFood shake providing 200 kcal: 15 g carbohydrates, 12.5 g protein, 8 g fat and 3 g fibre).

Breath VOC and glucose samples are collected every 15 min for approximately 90 min. For the remainder of the day, participants may consume self-selected meals or snacks according to their usual routine, with breath VOC and glucose sampling immediately beforehand. An overview of the study schedule is illustrated in figure 1, and the schedule is summarised in table 2.

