## Discussion

This study examines whether daytime changes in exhaled VOCs can be observed under controlled, real-world-compatible conditions and whether such changes differ across metabolic groups. Breath signatures in diabetes have shown promise, but reproducibility challenges remain. Time-of-day effects are plausible contributors and have not been systematically explored in diabetes research. A standardised breakfast and structured sampling allow evaluation of short-term metabolic responses, while participant-selected meals later in the day preserve ecological validity.

This work is exploratory and not powered for formal hypothesis testing. Instead, the intent is to generate data on temporal variation, effect size estimates and protocol considerations for future studies. Insights regarding sampling windows, fasting requirements and links to glucose or microbiota profiles may help refine breath-based metabolic monitoring approaches. If meaningful daytime variation emerges, time-locked sampling may be warranted; if not, breath analysis may offer greater flexibility than currently assumed.

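### With one visit and one breakfast at a near-fixed time, the planned assessment over time cannot tell time-of-day variation from the breakfast response, yet the interim rule calls the change circadian

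*Protocol article*

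**What the plan says.** **Outcome and analysis.** Under Outcomes: "The primary outcome is the temporal profile of VOC intensity across the 08:00–16:00 period". Under Data processing and analysis: "within-subject changes over time will be assessed using non-parametric repeated-measures approaches appropriate for the data structure". That section names no term for meals or time since intake, and no restriction to fasting or pre-meal samples.

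**Design.** Study design and setting: "Each participant completes one 8-hour study visit". Figure 1 legend: "Participants arrive fasting at 08:00, complete baseline assessments and consume a standardised breakfast". Study procedures adds two fasting breath samples before breakfast and then: "Breath VOC and glucose samples are collected every 15 min for approximately 90 min". After that, breath is sampled only just before each voluntary, self-selected meal or snack. The Figure 1 legend numbers these as meals 2–4.

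**Use of the result.** Under Sample size, an exploratory look after around 30 participants stops the study unless at least three VOCs show intensity changes, which the rule describes as circadian. The Discussion draws a consequence: "If meaningful daytime variation emerges, time-locked sampling may be warranted".

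**Meal records.** Table 2 describes the diary as "Diet and sleep diary (covering 2 days before visit"), returned on or after the visit. Data sources and documentation says "All data collection instruments and source documents are summarised in table 3", and Table 3 has no item for intake on the visit day. The Abstract says that later meals follow a structured timing, whereas Study procedures lets participants follow their usual routine.

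**The concern.** Everyone moves from fasted to fed in the same early part of the window, and most samples are taken there. A VOC that responds to the shake but has no time-of-day rhythm would still show a within-subject change over the day. Nothing in the stated analysis separates the two causes.

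This matters in two places. The interim rule is the only stop-or-continue criterion in the document, and a purely prandial signal could satisfy it. The Discussion moves from daytime variation to sampling at fixed clock times, but a prandial cause would point to controlling fasting status instead. More participants under the same schedule would not help, because the confounding lies in the design and not in the precision.

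**Working it through.** The protocol gives no effect size, SD, alpha or power, so it has no figure of its own to reproduce. The one arithmetic check agrees: 3 groups × about 10 = 30, which matches the interim look at around 30.

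**1. Where the samples fall.**
- Fasting: 2 (Study procedures).
- After breakfast: 90 / 15 = 6 (Study procedures).
- Later: at most about 3, assuming one before each of meals 2–4 (Figure 1 legend).
- Share between fasting and 90 minutes: (2 + 6) / (2 + 6 + 3) = 8 / 11 = 73%.

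If breakfast is at about 08:45 (assumed), this block ends at about 10:15. The remaining 345 of 480 minutes (72% of the window) rest on at most about three samples.

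**2. Clock time against time since breakfast.** For participant *i*, sample *j*: clock time = *Bᵢ* + time since breakfast, where *Bᵢ* is that participant's breakfast time. With one visit, *Bᵢ* is constant within a participant, so the within-participant correlation is exactly 1. Pooled over participants (simulated), it is 0.999, 0.991 and 0.963 for a breakfast-time SD of 5, 15 and 30 minutes.

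**3. Clock time against time since *last* intake.** Later meals reset this variable. With meals 2–4 assumed at about 10:45, 12:30 and 15:00 (SD 30 minutes), the within-participant correlation over the post-breakfast samples is 0.80–0.81. The variance inflation is 1 / (1 − r²): 2.75 at r = 0.798 and 2.95 at r = 0.813. Both terms can therefore be estimated, with a loss of precision.

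**4. How often a meal response alone looks like change over time.** All inputs here are assumptions:
- breakfast at 08:45 (SD 15 minutes) and later meals as in step 3;
- the two fasting samples entered as one, giving 10 time points;
- response to each meal A × (d/45) × exp(1 − d/45), with *d* minutes since that meal, so it peaks at 45 minutes with height A in residual SDs;
- between-participant SD equal to residual SD;
- time-of-day effect zero;
- Friedman test at 5%, 1,000 runs (Monte Carlo standard error at most √(0.25/1000) = 1.6 points).

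| Height A | All samples, n=30 | All samples, n=60 | Fasting + pre-meal only, n=30 | Fasting + pre-meal only, n=60 |
|---|---|---|---|---|
| 0 | 6% | 4% | 5% | 5% |
| 0.25 | 9% | 17% | 6% | 13% |
| 0.5 | 29% | 60% | 15% | 29% |
| 1.0 | 91% | 100% | 51% | 86% |

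The test holds its level when there is no meal response. Otherwise the rate depends on A. Using only the two fasting and six post-breakfast samples, the same response curve gives higher rates: 13% / 24% at 0.25 SD and 45% / 81% at 0.5 SD (n = 30 / 60).

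Restricting to fasting and pre-meal samples roughly halves the rate at 0.5 SD but does not bring it to 5%, because earlier meals still carry over. These are rates per VOC. The interim rule asks for three VOCs and is judged without a formal test, so they do not convert directly into a probability of continuing.

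**The case against.** **The outcome and the method are not wrong as worded.** The outcome is temporal variation, and a meal-driven change is temporal variation. The Discussion says that the breakfast and sampling allow short-term metabolic responses to be evaluated, and it lists fasting requirements among the expected insights. The analysis sentence leaves the method open, the Friedman test is not named, and a meal term could stand in an analysis plan that is not shown. Participants and eligibility also provides for descriptive adjustment for recent diet. All of this stands. It does not remove the point: no choice of test separates the two time scales within the first 90 minutes, and this document itself fixes the circadian criterion and the time-locked consequence.

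**A reader might infer that later meals go unrecorded and can never be separated out.** The documents do not support this. Each later meal is preceded by a required breath and glucose sample, so its start time can be recovered. Only meal content is absent from the listed instruments, and the full protocol and eCRF, which are not shown, may record it. Exact collinearity holds for time since breakfast, not for time since last intake.

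**A reader might infer that the study will report a meal response as a circadian finding.** That is too firm. At a meal effect of 0.25 SD the rate is 9–17%, and nothing in the documents says how large the effect is.

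**The stakes are limited.** The study is exploratory and disclaims formal inference. A mistaken decision to continue leads only to the maximum of 60 already planned. This lowers the weight of the interim error, but not that of the sampling conclusion.

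**Conclusion.** The point holds in this form: the design and the stated assessment over time cannot distinguish time-of-day variation from the breakfast response. A purely prandial change could therefore satisfy a rule worded as circadian and support a clock-time sampling conclusion.

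The collinearity with time since breakfast follows from the design and needs no assumption. The 73% share assumes three later samples. The size of the problem is not known: the illustrated rates run from 9% to 100% for meal effects of 0.25–1.0 SD at n = 30–60, under assumed meal times, response shape and variances. Time since last intake is only partly collinear with clock time (about 0.8 under the assumed meal times), so partial separation later in the day is feasible.

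**What to change.** 1. **Breakfast block.** Report the change from 0 to 90 minutes as a postprandial response, not as time-of-day variation.
2. **Time of day.** Model all samples on log or rank-transformed intensity with a participant random intercept and separate terms for clock time and time since last intake. State how the fasting samples are coded. Use fasting versus later pre-meal samples as a supporting contrast only, since it reduces the confounding without removing it.
3. **Interim rule.** In Sample size, replace circadian by time-of-day changes, judged from the analysis in step 2.
4. **Discussion.** State that clock time and the breakfast response are only partly separable, so that a conclusion on time-locked sampling may not rest on the pooled profile.
5. **Records.** Take meal start times from the pre-meal samples. Confirm that the visit-day eCRF records meal content, which Tables 2 and 3 do not list. Reconcile the Abstract's structured timing of later meals with the usual routine in Study procedures.

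The cost is wording, a modest amount of analysis work and possibly one short form. The time-of-day estimate will be less precise than a test on all samples, because it draws its information mainly from the few later ones. It also assumes that self-selected meals act on VOCs much as the breakfast does. The change is best made before the interim look. The article reports data from three participants before the pause and no interim analysis so far.

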### Patient and public involvement

This study was not developed through a dedicated patient advisory panel, but its research question and design were informed by continuous interactions with people living with diabetes in the clinical and research environment of the Department of Diabetes, Endocrinology, Nutritional Medicine and Metabolism and the DCB foundation. Both institutions maintain close connections with the diabetes community and regularly organise patient engagement events where individuals with lived experience provide feedback on research relevance and feasibility. Beyond the clinical setting, the research team contributes to broader public engagement through the University of Bern’s science fairs, Clinical Research Day and the national Future Day for school children. Findings from this project will be shared at future DCB patient engagement events and public science days to foster dialogue and mutual learning between researchers, patients, healthcare professionals and the wider community.

### Ethics and dissemination

The study complies with the Declaration of Helsinki and the Swiss Human Research Act/Ordinance. Ethics approval was granted by the Ethics Committee of the Canton of Bern (BASEC 2023-01143) and is registered on ClinicalTrials.gov under NCT05984979. Written informed consent is obtained from all participants before any study procedures. As this is a non-invasive observational study involving breath sampling and questionnaires, no major risks are anticipated; any adverse events will be documented.

Results will be disseminated through peer-reviewed publications, conference presentations and lay summaries. Deidentified data and analysis code will be deposited in Zenodo/Dryad and GitHub after study completion in accordance with institutional and repository policies.

## Discussion

This study examines whether daytime changes in exhaled VOCs can be observed under controlled, real-world-compatible conditions and whether such changes differ across metabolic groups. Breath signatures in diabetes have shown promise, but reproducibility challenges remain. Time-of-day effects are plausible contributors and have not been systematically explored in diabetes research. A standardised breakfast and structured sampling allow evaluation of short-term metabolic responses, while participant-selected meals later in the day preserve ecological validity.

This work is exploratory and not powered for formal hypothesis testing. Instead, the intent is to generate data on temporal variation, effect size estimates and protocol considerations for future studies. Insights regarding sampling windows, fasting requirements and links to glucose or microbiota profiles may help refine breath-based metabolic monitoring approaches. If meaningful daytime variation emerges, time-locked sampling may be warranted; if not, breath analysis may offer greater flexibility than currently assumed.

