**Trial registration number:**

NCT05984979.

STRENGTHS AND LIMITATIONS OF THIS STUDYControlled yet pragmatic single-day design enables assessment of daytime variation in exhaled volatile organic compounds (VOCs) under near-real-world conditions.Inclusion of participants without diabetes, with type 1 diabetes and with type 2 diabetes enables cross-group comparison of metabolic influences.Multimodal sampling (breath VOCs, glucose, body composition, oral and stool microbiota) supports integrative analyses.Exploratory nature and modest sample size limit formal inference; findings will primarily inform future powered studies.Dependence on a single gas chromatography–ion mobility spectrometry system instrument introduces vulnerability to device downtime and scheduling delays.

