## Introduction

 Breath volatile organic compounds (VOCs) arise from endogenous metabolism, microbial activity and environmental exposures, and have been evaluated as non-invasive markers in metabolic and inflammatory contexts.^1^,^4^ In diabetes research, altered levels of VOCs such as ethanol, isopropanol, dimethyl sulfide, isoprene and pentanal have been reported in individuals with type 1 diabetes (T1D) compared with individuals without diabetes.^5^ Other studies suggest associations between exhaled acetone, methyl nitrate, methanol, propane and circulating glucose,^6^ and hypoglycaemia-linked breath signatures have been observed.^7 8^ However, these findings are not uniform. Some investigations identified glucose–acetone correlations, whereas others did not.^9 10^ Heterogeneity in analytical platforms, diet, gut microbiota composition and function, metabolic status and sampling procedures likely contributes to these inconsistencies.^11^ Despite these limitations, breath VOC analysis holds potential as a non-invasive adjunct to existing biomarkers, offering real-time metabolic information relevant to glycaemic monitoring, early detection of dysglycaemic states, disease stratification and potentially early identification of metabolic dysregulation in populations at risk for or with undiagnosed type 2 diabetes (T2D),^11 12^ though superiority over established markers has not yet been demonstrated.

Circadian physiology may also influence breath VOC patterns. Hormonal rhythms, eating behaviour, nutritional composition and microbial metabolism vary across the day.^11^,^14^ Breath studies in respiratory medicine have shown time-of-day differences in specific exhaled metabolites.^15^ Yet, in diabetes research, sampling times are rarely standardised, and circadian effects are seldom considered.^5^,^79 10^ If temporal variation exists, ignoring it may obscure clinically meaningful signals; if minimal, sampling may be more flexible than assumed.

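### The Discussion has no inconclusive branch: if meaningful variation does not emerge, the result points to flexible sampling, although that null arises mainly from the smaller, stopped sample

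*Protocol article*

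**What the plan says.** The Discussion sets out how the result will be read: "If meaningful daytime variation emerges, time-locked sampling may be warranted; if not, breath analysis may offer greater flexibility than currently assumed". The part at issue is the second half, "if not, breath analysis may offer greater flexibility than currently assumed". Just before this, in the same paragraph, it states: "This work is exploratory and not powered for formal hypothesis testing". The strengths and limitations list agrees: "Exploratory nature and modest sample size limit formal inference; findings will primarily inform future powered studies".

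The Sample size section gives the numbers: "A total of up to 60 participants will be enrolled, initially targeting approximately 10 per group". With three groups that is about 30 people, the point at which an exploratory look takes place. The rule at that look is: "If no circadian intensity changes are observed in at least three VOCs, the study will be stopped early". Otherwise recruitment continues to 60. The section says that no formal testing and no statistical stopping rule apply.

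The rule's apparent meaning is that the study stops when fewer than three VOCs show a change, that is, with none, one or two.

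**The concern.** The Discussion sentence has two branches and no third. Every outcome short of meaningful variation emerging falls into the branch that favours flexible sampling times. Not observing variation is different from showing that variation is small, and an imprecise study can do the first without the second.

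The stopping rule sharpens this. A study that goes on to 60 has, by construction, already shown changes in at least three VOCs. A study-level null is therefore the stopped study of around 30, so the reading that most needs precision is made with the least.

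The Introduction explains what is at stake: if temporal variation is real, ignoring it may hide clinically relevant signals. A null read too generously would lend some support to leaving sampling times unstandardised.

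**Working it through.** **Inputs from the Protocol article.** Interim look at around 30; maximum 60; continue only if at least three VOCs change (Sample size). Within-person change over time, assessed by non-parametric repeated-measures methods (Data processing and analysis). The article states no alpha, power, effect size or SD behind 30 or 60, so there is no sponsor calculation to reproduce. The one arithmetic check, 3 groups × about 10 = about 30, agrees with the timing of the look.

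**Assumptions.** One paired contrast (later time minus fasting) per VOC, all participants pooled. A paired t-test stands in for the non-parametric test. Effect d = mean change / SD of change. Two-sided alpha 0.05 with no correction for many VOCs.

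**Precision.** 95% half-width in SDs of the change = t(0.975, n−1)/√n.
- n = 30: 2.045/5.477 = 0.37
- n = 60: 2.001/7.746 = 0.26

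**Power.** 1 − F(t; n−1, d√n) + F(−t; n−1, d√n), where F is the non-central t distribution function and t the two-sided critical value.

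| d | n = 30 | n = 60 |
|---|---|---|
| 0.2 | 0.185 | 0.332 |
| 0.3 | 0.355 | 0.628 |
| 0.4 | 0.563 | 0.862 |
| 0.5 | 0.754 | 0.968 |
| 0.8 | 0.988 | 1.000 |

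With alpha 0.0025 (Bonferroni for an assumed 20 VOCs), power at n = 30 falls to 0.066 for d = 0.3 and 0.309 for d = 0.5.

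**Chance of stopping although VOCs truly vary.** P(X < 3) with X ~ Binomial(K, power at n = 30), for K truly varying VOCs treated as independent, alpha 0.05.

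| d | K = 3 | K = 5 | K = 10 |
|---|---|---|---|
| 0.2 | 0.994 | 0.953 | 0.722 |
| 0.3 | 0.955 | 0.756 | 0.250 |
| 0.4 | 0.822 | 0.383 | 0.023 |
| 0.5 | 0.571 | 0.099 | 0.000 |
| 0.8 | 0.034 | 0.000 | 0.000 |

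These figures count only the K varying VOCs. If many unchanging VOCs are also screened at nominal 5%, false positives would make continuation more likely: with 50 independent unchanging VOCs, the chance of three or more is 0.459.

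**What it takes to show that change is small.** Two one-sided tests (TOST) at 5%, 80% power, true change zero: n = ((1.645 + 1.282)/margin)². This gives 35 for a margin of 0.5 SD, 96 for 0.3 SD and 215 for 0.2 SD. Turned round, the smallest margin that can be shown is 2.926/√30 = 0.53 SD with 30 people and 2.926/√60 = 0.38 SD with 60. The margins are illustrative.

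**Sampling.** After the first 90 minutes or so, breath is sampled only before self-selected meals or snacks (Study procedures). If fewer than 30 people contribute at a given later time, the interval there is wider than ±0.37 SD.

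**The case against.** The strongest reply is that the Discussion sentence is hedged. It says may, it conditions on meaningful variation, and it sits beside a plain statement that the study is unpowered and aims at effect-size estimates. This stands as to tone: the article announces no firm claim, and nothing in it predicts that a null will be published as an endorsement of unstandardised sampling. But hedging does not supply the missing third outcome, because a wide interval supports neither branch.

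A second reply is that a condensed article may leave interval reporting and any bound to the statistical analysis plan. That also stands, and the absence of a bound is not the fault raised here. The fault is the two-way reading that the article itself prints.

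Several stronger readings are tempting and are not supported:
- *The Introduction makes the same error.* Its clause, "if minimal, sampling may be more flexible than assumed", is a conditional about the true size of the variation. It infers nothing from non-detection.
- *The study stops exactly when nothing is seen.* The rule applies at around 30 and appears to stop with up to two VOCs changing. Nor does the Sample size section itself tie a stop to flexible sampling.
- *The null rests on 10 people per group.* For n = 10 the half-width is 0.72 SD and power at 0.5 SD is 29%, but these describe group-specific profiles. The primary outcome is temporal variation, to which about 30 people contribute; group comparison is secondary.
- *A null can support nothing.* Thirty people can exclude large mean changes.
- *The paired fasting breaths supply the bound.* The plan says "Two fasting breath samples and one capillary glucose measurement are then collected" and does not call the two samples replicates. More important, a repeatability limit concerns an individual's difference, not a mean change. If the SD of change is √2 × the within-person SD, the limit 1.96 × √2 × within-person SD equals 1.96 SD of change. With a 90% half-width of 0.31 SD at n = 30, an observed mean shift up to 1.96 − 0.31 = 1.65 SD would pass as minimal. If the SD of change is twice that, shifts up to 0.98 − 0.31 = 0.67 SD still pass.

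**Conclusion.** The point holds in a limited form. The Discussion lets non-emergence of meaningful variation point to flexible sampling, and the stopping rule means that an overall null comes from around 30 participants. At that size a true 0.3 SD mean change would be missed about 64% of the time (1 − 0.355) and a 0.5 SD change about 25% (1 − 0.754), while large changes could be excluded. A stopped study may also hold one or two VOCs that do vary.

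The sizes rest on assumed effects, a single paired t contrast, nominal 5% and no multiplicity correction. Repeated samples per person could improve precision; correction for many VOCs or sparse later sampling would reduce power or precision. The need for an inconclusive outcome does not depend on the exact figures. The consequence is confined to what a null may be said to show; the design and data collection are unaffected.

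**What to change.** 1. Report each VOC's within-person change from fasting to later times with a confidence interval.
2. Before the interim look, set a bound for a relevant mean change. Do not take the individual repeatability limit from the two fasting samples as that bound.
3. Reword the Discussion so that the flexibility statement applies only to VOCs whose interval lies inside the bound, and so that an early stop, or an interval extending beyond the bound, is reported as not determined.
4. Leave the Introduction as it is.

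This needs no new participants, visits or samples and fits the stated aim of effect-size estimation. It can still be done in time: the Study design and setting section reports three completed participants before the pause and no interim analysis so far. The cost is a less favourable null statement: more VOCs, and any stopped study, will end as inconclusive.
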